### The Netherlands vs. Germany

Differences in means, at 3 and 6 months of follow-up, between the Dutch dr. Bart group (B) versus the German dr. Bart group (C) will be explored by mixed model repeated measures analyses with a random intercept, including country (i.e. the Netherlands or Germany), accompanying baseline value and interaction between country and time. Analyses will be corrected for relevant confounders; age, gender and BMI among others.

### Use of the app and its relation with clinical outcomes

The relation between clinical outcomes and use of the app will be studied using multivariable regression analyses with clinical outcome (e.g. physical functioning, PA) as the dependent variable, whereas quantitative data about use of the app will serve as independent variable(s). We hypothesize that participants who more frequently use the dr. Bart app will improve more on clinical outcomes (e.g. physical functioning) compared to less frequent and non-users. Additionally, a Kaplan-Meier curve will be constructed to illustrate the proportion of persons who start using the app (i.e. who have chosen at least one goal) over time.

### Economic evaluation from the health care perspective

The economic evaluation is based on the general principles of cost-utility analysis (CUA) and cost-effectiveness analysis (CEA), applying a health care perspective. Direct medical cost in the Netherlands due to OA in the 6 months of follow-up will be analysed, in both primary and secondary care and will be measured retrospectively by online questionnaires on a 3 month recall basis. Standard cost prices of the Dutch costing guideline will be used [54]. To determine the incremental cost-effectiveness ratio (ICER) for the CUA, differences in costs between the usual care group (A) and the dr. Bart group (B) will be divided by differences in QALYs. For the CEA, differences in costs between the groups (A vs. B) will be divided by the differences in secondary outcomes (e.g. physical functioning, physical activity). Uncertainty (95% CI (confidence interval)) around the ICERs will be stochastically determined by the bootstrap method.

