#### Randomization, allocation concealment and blinding

Dutch consenting participants will be randomly allocated by the researcher to usual care (A) or dr. Bart (B) (allocation ratio 1:1) after completing baseline assessment performed with CastorEDC. CastorEDC uses a validated variable block randomization method (with randomly varying block sizes of 2, 4 and 6) and is stratified on the individual level by hip or knee OA. The researcher who will ascertain randomization will be concealed for treatment allocation. Due to the design of this study, blinding of participants and researchers is not possible. Data collectors will be blinded as data will be collected with validated questionnaires via CastorEDC. All German participants receive the dr. Bart app during the study (C), see Fig. 2.

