### Measurements

Three self-assessed sets of online questionnaires (at baseline and, 3 and 6 months after inclusion) will be collected with CastorEDC, (Table 1) and, where applicable, a reminder will be sent after 1 week. Participants will not receive (financial) incentives or other compensation for completion of the questionnaires or the study.

**Table 1 Tab1:** Assessments in the Netherlands (arm A + B) and in Germany (arm C) at baseline and at follow-up of 3 and 6 months

	Baseline assessment (T0)	Follow-up 3 months (T3)	Follow-up 6 months (T6)
Patient characteristics (A + B + C)	X		
Cost questionnaire (A + B)	X	X	X
PAM-13 (A + B + C)	X	X	X
EQ-5D-3 L (A + B + C)	X	X	X
HOOS/KOOS (A + B + C)	X	X	X
SQUASH (A + B + C)	X	X	X
TOA (A + B + C)	X	X	X
IPQ-K (A + B + C)	X	X	X
OA-QI (A + B + C)	X	X	X
SUS (B + C)		X	X
Use of app (B + C)		X	X

*Abbreviations*: *PAM-13*, Patient activation measure, *EQ-5D-3 L* Euro Quality of Life – 5 Dimensions - 3 Level, *HOOS/KOOS* Hip/Knee Osteoarthritis Outcome Score, *SQUASH* Short Questionnaire to assess health-enhancing physical activity, *TOA* Treatment beliefs in knee and hip osteoarthritis, *IPQ-K* Illness Perception Questionnaire, *OA-QI* Osteoarthritis Quality Indicators, *SUS* System Usability Scale

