#### Secondary study parameters

Secondary study parameters include direct medical costs, self-management behaviour, health-related quality of life, physical function (in daily living, sport and recreation), physical activity, treatment beliefs in OA, illness perception, perceived quality of care, and use and usability of the dr. Bart app.

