### Efficacy

Differences in the primary and secondary outcomes between the two arms of the RCT in the Netherlands (A vs. B) after 3 and 6 months will be assessed by either linear mixed models or Poisson regression, as appropriate, with a random intercept, including treatment group (i.e. usual care (A) or dr. Bart (B)), baseline value and interaction between treatment group and time as covariates. The primary outcome in the Netherlands will be reported as an incidence rate ratio in case of Poisson regression, or negative binomial regression, as appropriate.

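### The economic evaluation states no baseline adjustment for incremental costs and QALYs, although baseline EQ-5D-3L and OA costs are collected in both arms; adjusting would gain precision at no cost

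*Protocol article*

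**What the plan says.** The section on the economic evaluation defines the cost-utility ratio in one clause: "differences in costs between the usual care group (A) and the dr. Bart group (B) will be divided by differences in QALYs". Uncertainty "around the ICERs will be stochastically determined by the bootstrap method". Costs cover the 6 months of follow-up and "will be measured retrospectively by online questionnaires on a 3 month recall basis". The section does not say how either difference is estimated or how QALYs are formed from EQ-5D-3L. It does not point to any model elsewhere in the article.

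The Efficacy section sets the models for "Differences in the primary and secondary outcomes between the two arms of the RCT in the Netherlands (A vs. B") at 3 and 6 months. These are linear mixed or count models with a random intercept that include "baseline value and interaction between treatment group and time as covariates". The section comparing the Netherlands with Germany also names the baseline value as a covariate.

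The list of secondary parameters begins: "Secondary study parameters include direct medical costs, self-management behaviour, health-related quality of life". QALYs are not on it.

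Table 1 under Measurements marks the row "Cost questionnaire (A + B") at baseline, 3 and 6 months, and EQ-5D-3L at the same three visits in all arms. Dutch participants are randomised with "allocation ratio 1:1", stratified by hip or knee OA.

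**The concern.** Both other between-arm analyses in the article name a baseline covariate; the economic one does not. A 6-month QALY computed as the area under the utility curve contains the baseline utility itself and is correlated with it through the later visits. Randomisation balances baseline utility and cost only on average, because neither is a stratification factor. An analyst who follows the economic section literally could take simple arm differences and leave the baseline measurements unused.

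The cost would be a wider interval than the data require, and a point estimate that carries whatever baseline gap happens to arise in this one trial. There is also a consistency issue. The cost-effectiveness ratios divide by differences in secondary outcomes such as physical functioning. As written, the same outcome could have a baseline-adjusted difference under Efficacy and a different one in the ratio.

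**Working it through.** **Plan's own figure.** No figure is given for the economic evaluation, so only the sample size can be reproduced. It is used below as an input. With a difference of 0.35, SD 1.00, two-sided alpha 0.05 and power 0.80: n = 2 × (1.96 + 0.8416)² / 0.35² = 128.1, so 129 per arm, as stated. Then 129 / 0.80 = 161.25, stated as 161.

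**Inputs.**
- From the article: 129 per arm with follow-up; EQ-5D-3L at 0, 3 and 6 months; costs at baseline and follow-up.
- Assumed, because the article gives no values: trapezoid QALY; equal utility SD s and equal correlation r between all visits; s = 0.20 (range 0.15 to 0.25); r = 0.4 to 0.7; correlation c between baseline and follow-up cost of 0.3 to 0.7. The small loss of degrees of freedom from adjustment is ignored.

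**QALY.** Q = 0.125·u0 + 0.25·u3 + 0.125·u6.
- Variance: s² × (0.09375 + 0.15625·r).
- Slope of Q on u0: 0.125 + 0.375·r.
- Share of variance explained by u0: R² = slope² / (0.09375 + 0.15625·r).
- Adjusted SE / unadjusted SE = √(1 − R²). This does not depend on s.

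| r | slope | R² | √(1 − R²) | SE reduction |
|---|---|---|---|---|
| 0.4 | 0.2750 | 0.484 | 0.718 | 28% |
| 0.5 | 0.3125 | 0.568 | 0.657 | 34% |
| 0.6 | 0.3500 | 0.653 | 0.589 | 41% |
| 0.7 | 0.3875 | 0.739 | 0.511 | 49% |

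At s = 0.20 and r = 0.6 the unadjusted SE of the QALY difference is √(2 × 0.04 × 0.1875 / 129) = 0.0108. The adjusted SE is 0.0108 × 0.589, about 0.0064.

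**Chance imbalance.** The SE of the baseline utility difference is 0.20 × √(2/129) = 0.0249. A one-SE imbalance moves the unadjusted QALY difference by 0.35 × 0.0249 = 0.0087 at r = 0.6. The 95% range of this carry-over is 1.96 × 0.0087 = ±0.017. Over s = 0.15 to 0.25 and r = 0.4 to 0.7 it runs from ±0.0366 × 0.275 = ±0.010 to ±0.0610 × 0.3875 = ±0.024.

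**Costs.** SE ratio = √(1 − c²).
- c = 0.3: 0.954, a 5% reduction.
- c = 0.5: 0.866, a 13% reduction.
- c = 0.7: 0.714, a 29% reduction.

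**The case against.** The economic section never calls the differences raw or unadjusted. It defines a ratio, and adjusted increments fit that definition equally well. The Efficacy section prescribes baseline adjustment for secondary outcomes, and direct medical costs and health-related quality of life are both listed as such, so adjustment may already be intended. A condensed article also commonly leaves the economic model to the full protocol or analysis plan.

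Much of this stands. A reader might infer that the plan discards the baseline data and divides crude differences; the text is silent and does not say so. A reader might also infer that the ratio would be biased. The article does not support that either: under 1:1 randomisation the simple difference is unbiased over repeated trials, and the bootstrap carries the variability that chance imbalance adds.

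It is also tempting to claim that imbalance could swamp the effect, but that depends on a gain the article does not state. If utility rose by 0.03 at both follow-ups, the gain would be 0.375 × 0.03 = 0.01125 QALY, and a one-SE imbalance would be 77% of it. With a rise of 0.06 the gain is 0.0225 and the share is 39%.

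What the objection does not settle is the link between the two sections. The efficacy models work visit by visit, with a random intercept and a group-by-time term. A QALY is one cumulative value per person, is not among the listed outcomes, and the economic section does not refer back. The efficacy models therefore cannot be applied to the ratio without a further decision.

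**Conclusion.** The point holds as a free gain in precision and clarity, not as an error. The economic section states no baseline adjustment and no link to the Efficacy models, while the baseline data needed are collected in both arms. If simple differences were used, the estimate would be valid but less precise, and open to chance baseline imbalance in the realised trial. The gain is substantial for QALYs and modest to moderate for costs: SE reductions of about 28% to 49% and about 5% to 29% respectively. Both ranges rest on the assumed correlations, and the first also on the trapezoid QALY; neither comes from the article. If the full protocol or analysis plan already specifies the adjustment, only a cross-reference is needed.

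**What to change.** Add one sentence to the economic evaluation section. It should say that incremental QALYs and incremental costs are each estimated by regression on treatment arm, adjusted for baseline EQ-5D utility and baseline OA cost respectively, plus the hip/knee stratum. It should add that both regressions are refitted within each bootstrap resample, with participants as the resampling unit so that the cost–QALY correlation is kept. For the cost-effectiveness ratios, say that the outcome differences are baseline-adjusted in the same way. The cost is this wording and minor programming. No new data, visits or participants are needed, because both instruments are already in the baseline assessment.

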Modern persuasive technologies (e.g. applications) offer the possibility to enhance goal setting and provide tailored information to people with OA that suits individual preferences and to enhance self-management at all times [31, 32]. Moreover, modern technologies can monitor health behaviour and provide real-time feedback, which are considered important elements of self-management [15, 33]. Although the use of modern technologies seems promising, the majority of eHealth applications have not proven their effectiveness in clinical trials [34–38], especially in the field of OA. Therefore, we iteratively and systematically developed a standalone e-self-management application (dr. Bart app) in both Dutch and German language, incorporating education, setting achievable health behaviour goals and provision of feedback. This paper describes the design of a study that aims 1) To evaluate the short term effects (after 3 & 6 months) of use of the dr. Bart app in terms of (self-reported) number of consultations in secondary health care due to OA of the knee and/or hip in the Netherlands. We hypothesize that the app is (cost-)effective compared to usual care. 2) To explore differences in use, usability and clinical outcomes between the Netherlands and Germany. This paper also describes the systematical and iterative development of the dr. Bart app.

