#### Experimental intervention groups (arms B and C)

Participants allocated to the Dutch intervention group (B) and all German participants (C) will receive the dr. Bart app (version number 1.3.7) for 6 months. They can use the dr. Bart app “ad libitum”. The app is only accessible for users after the researcher has provided access for the app. Throughout the study, participants are able to call and send emails to the researcher when they have questions regarding the dr. Bart app or the study.

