### Assessments

#### Direct medical costs

By means of an OA specific questionnaire direct medical costs (i.e. healthcare-related) due to OA in the 6 months of follow-up will be collected, in both secondary and primary healthcare. Standard cost prices of the Dutch costing guideline will be used [54]. Direct medical costs will be computed by multiplying the cost prices with the usage frequency as reported by participants.

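### A bootstrap 95% CI on the ICER cannot be read if the effect difference is near zero, and the costs named for the ICER do not cover the app itself

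*Protocol article*

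**What the plan says.** The section on the economic evaluation plans a cost-utility analysis in which "differences in costs between the usual care group (A) and the dr. Bart group (B) will be divided by differences in QALYs", and a cost-effectiveness analysis in which the cost difference is divided by a difference in a secondary outcome such as physical functioning or physical activity. Both take a health care perspective. The summary of uncertainty is fixed for both ratios: "Uncertainty (95% CI (confidence interval)) around the ICERs will be stochastically determined by the bootstrap method". That section names no cost-effectiveness plane, net monetary benefit, acceptability curve or willingness-to-pay threshold.

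On costs, the same section says: "Direct medical cost in the Netherlands due to OA in the 6 months of follow-up will be analysed, in both primary and secondary care", at Dutch guideline prices. The section Direct medical costs gives the rule: "Direct medical costs will be computed by multiplying the cost prices with the usage frequency as reported by participants". Arm B "will receive the dr. Bart app (version number 1.3.7) for 6 months" and may phone or e-mail the researcher with questions. No section attaches a cost to the app.

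Cost-effectiveness is part of the stated hypothesis at the end of the Background: "We hypothesize that the app is (cost-)effective compared to usual care".

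**The concern.** A ratio loses its meaning as a scale when its denominator can change sign. A negative ICER can come from a saving with a health gain or from an extra cost with a health loss. A positive ICER can come from paying more for a gain or from saving money at the price of a loss. Two limits on the ICER scale cannot keep these cases apart, so the reported interval could mix opposite conclusions.

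A small denominator is realistic here. The Background describes the benefits of traditional self-management programmes over usual care as small, follow-up lasts 6 months, and the trial is sized on consultations rather than on any of the ICER denominators.

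The second issue is the numerator. A participant can report visits and treatments but not hosting, maintenance or user support. If the costing rule is applied as written, arm B carries no cost for its intervention and the incremental cost is too low by that amount.

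**Working it through.** **Inputs from the article (Sample size).** Difference 0.35 consultations, SD 1.00, power 0.80, two-sided alpha 0.05, 129 evaluable and 161 included per arm.

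**Reproducing the stated figure.** n = 2 × (1.96 + 0.8416)² × 1.00² / 0.35² = 128.1, rounded up to 129. Allowing for 20% loss, 129 / 0.8 = 161.25, stated as 161. The sample size is not in dispute; it supplies the precision of the A versus B comparison.

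**Sign ambiguity.** −50 / +0.01 = −5,000 (cheaper and better). +50 / −0.01 = −5,000 (dearer and worse).

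**Precision without assuming an SD.** The SE of a standardised difference is √(2/129) = 0.1245, ignoring baseline adjustment. For a true effect of 0.2 SD, the lower end of the range that the Sample size section gives for its primary outcomes, z = 0.2 / 0.1245 = 1.61. The 95% interval for the denominator then includes zero with probability Φ(1.96 − 1.61) − Φ(−1.96 − 1.61) ≈ 64%. At 0.1 SD it is about 87%. This applies to QALYs, function and activity alike.

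**QALY illustration.** The article gives neither a QALY SD nor an expected gain, so both are assumed and varied. SE = SD × √(2/129), and the share of replicates with a negative denominator is Φ(−gain / SE).

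| True gain | SD 0.06 (SE 0.0075) | SD 0.10 (SE 0.0125) | SD 0.12 (SE 0.0149) |
|---|---|---|---|
| 0 | 50% | 50% | 50% |
| 0.005 | 25% | 34% | 37% |
| 0.01 | 9% | 21% | 25% |
| 0.02 | 0.4% | 5.4% | 9% |
| 0.03 | 0.0% | 0.8% | 2.2% |

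**Effect on the interval.** One constructed data set per scenario, 129 per arm and 5,000 bootstrap replicates. Assumed: QALY SD 0.10, cost difference −50, cost SD about 600 (currency units), and percentile limits.

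| QALY gain | 95% limits for the ICER | Replicates with negative denominator |
|---|---|---|
| 0.01 | about −66,000 to +65,000 | 22% |
| 0.03 | about −14,900 to +6,400 | 0.5% |
| 0.06 | about −4,000 to +1,900 | none |

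At a gain of 0.01 all four quadrants of the cost-effectiveness plane are occupied: dearer and better 23%, cheaper and better 55%, dearer and worse 7%, cheaper and worse 15%. The two limits convey none of this. At 0.06 every denominator is positive and the interval can be read.

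**App cost.** A per-user cost c adds exactly c to the B minus A cost difference. With an assumed saving of 50, c = 25 leaves −50 + 25 = −25, c = 50 gives 0, and c = 100 gives +50. The article gives no value for c.

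**The case against.** **The article does not say that ICERs will be sorted and percentiles taken.** True. It does commit to a 95% CI around the ICERs, and any pair of limits on that scale inherits the sign ambiguity. A full protocol or SAP may add a plane or an acceptability curve, so the point is that the stated summary is badly chosen, not that better ones will never be used.

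**The problem depends on the size of the effect.** This stands. A reader might infer that the interval is meaningless whatever the result. The second table shows otherwise.

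**A reader might infer that the cost-effectiveness hypothesis could be neither supported nor refuted.** The article does not support that. Direct medical costs and quality of life are secondary parameters (Secondary study parameters), and the Efficacy section compares secondary outcomes between A and B outside any ratio, although it does not name QALYs. Nor would the replacement necessarily settle the question. With an assumed gain of 0.005, QALY SD 0.10, saving 50, cost SD 600, independent costs and effects, and a threshold of 20,000, net benefit is 20,000 × 0.005 + 50 = 150. Its SE is 0.1245 × √(600² + 2,000²) ≈ 260, so its 95% CI includes zero in about 91% of trials. Low precision for a small effect is a separate matter from the choice of summary.

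**A reader might infer that the plan prices the app at zero.** No section says so. The costing rule appears under direct medical costs and defines that component. An intervention price may be left to a fuller document. The app is standalone and fully automated, part of the contact with the researcher is study support, and the article does not say who pays for hosting. All of this stands and limits the weight of the point. It remains that the only costs named for the ICER are those participants report.

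**Conclusion.** The concern holds conditionally. The article fixes a 95% CI on a ratio, and that interval is not interpretable when the effect difference is small relative to its SE. Under the assumed QALY SDs with 129 per arm, the problem is substantial for true gains up to about 0.01 (9% to 50% negative replicates), moderate at 0.02 (0.4% to 9%), and slight from 0.03 (at most 2.2%). How likely a small gain is cannot be settled from the article, which gives no expected QALY difference or SD.

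The app cost is a secondary correction. As written, the costs entering the ICER cannot capture it. The size of the omission is unknown and may be small, but its direction favours arm B.

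Both points concern a secondary analysis.

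**What to change.** Replace the CI around the ICER with summaries taken from the same bootstrap replicates, resampling each participant's costs and effects together:

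- incremental costs and incremental effects, each with a 95% CI;
- the cost-effectiveness plane;
- for the cost-utility analysis, incremental net monetary benefit with a 95% CI over a range of thresholds stated in advance;
- an acceptability curve.

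The ICER can stay as a point estimate. Add to every arm B participant a per-user app cost covering hosting, maintenance and non-research support, as far as these fall under the health care perspective, with a low and a high value as sensitivity analysis. If a component is left out because it falls outside that perspective, say so.

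The cost is small: no new participant data, the same bootstrap output, a stated threshold range, and one unit cost from the app developer. The cost result may become slightly less favourable to the app. The change makes the uncertainty readable but does not add precision. It should be fixed before the cost data are analysed by arm.

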### Timeline

The development of the dr. Bart app was finished at the end of 2017. Recruitment of participants in the Netherlands is ongoing as of January 2018. Participants will be included until the required sample size is acquired. For the German part of the study, we will start recruiting participants as of June 2019.

